### Sample size

Until now, no trials and, therefore, no specific effect size of the selected interventions for this specific population are present in the peer-reviewed literature. Our sample size calculation of 45 patients per study arm is based on a difference of 6 points in the primary endpoint of the FSS-ICU sum score between the parallel groups after 2 weeks of treatment. We assume an alpha level of 5%, a statistical power of 80% (beta = 20%) and a standard deviation (SD) of 10 using a two-sample *t* test for mean differences. Our assumption is based on the theory that the one experimental group achieves a mean of 22 points and the other group achieves a mean of 16 points in the FSS-ICU test assuming a SD of 10 in the FSS-ICU sum score and assuming that the rate of recovery of walking ability will be 0.6 in the one and 0.4 in the other group. We used the SAS (SAS Institute Inc., Cary, NC, USA) power and sample size programme for our sample size calculation. Because we consider a 20% dropout rate, a total of 108 patients (54 per study arm) would be enrolled to ensure 45 subjects in both intervention arms.

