### Statistical methods

We will conduct both intention-to-treat and per-protocol analyses, with the intention-to-treat analysis being always the primary analysis for the primary and secondary outcomes.

Our descriptive statistics will include means and SDs, medians and interquartile ranges for continuous variables, and the number and proportions for categorical variables as appropriate [39].

We will compare the two intervention groups at baseline regarding characteristics and demographics, using two-tailed Student’s *t* tests or Fisher’s exact tests, as appropriate. Variables that differ between the groups at baseline will be considered as possible confounders and adjusted for in subsequent analyses. The global alpha level will be set at 0.05 for all comparisons. To avoid multiplicity we will use a Tukey-Kramer alpha adjustment for multiple comparisons of the same outcome. Skewed data will be analysed with nonparametric test alternatives (e.g. we will use the Mann-Whitney *U* test instead of Student’s *t* tests if data are skewed).

For the primary endpoint, the FSS-ICU, we will test the hypothesis that the sum score after 2 weeks of intervention and at follow-up will be statistically different between groups. We will consider a minimum difference of 5 points of the FSS-ICU sum score (range 0–35 points) between groups as being clinically important.

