### Ethics and dissemination

The FITonICU study will be conducted in accordance with the Helsinki Declaration. The study is noninvasive, imposes no additional risk on patients, seems to have enough power to detect meaningful determinants and our protocol has been approved by the medical ethical committees (ethical vote ‘Landesärztekammer Sachsen’ Germany; EK-BR-104/15-1). Furthermore, written informed consent is obtained from all participants or, if necessary, from a legal guardian ([name]). We registered our study on 6 April 2016 before enrolling the first patient in the trial at the German Clinical Trials Register (www.germanctr.de/) with the identifier DRKS00010269.

We plan to disseminate the results of this study to the scientific, medical and general public by publication in national and international peer-reviewed journals, as well as by presentations at conferences and meetings with clinicians working with patients with ICUAW.

Authorship will follow the recommendations of the International Committee of Journal Editors for authorship. No professional writers will be employed.

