### Limitations

One could argue that the lack of a true control group, e.g. of standard or no additional physiotherapy, might be a weakness of our trial protocol. We have, however, designed this study to compare two potentially capable and reasonable active physical rehabilitation interventions for patients on ICU. The feasibility and safety of BEDCYC was established in previous studies [37] and is a promising physical rehabilitation intervention for patients on ICU. The efficacy and effectiveness relative to standard treatment alone for BEDCYC will be investigated in other RCTs [37, 50]. The MOBILITY intervention is not yet described in the literature, but MOBILITY was tested over several months at our department and seems a feasible physical rehabilitation intervention for patients on ICU. We decided not to introduce a ‘classical’ control group in our study, because there is no such classical control treatment in the ICU, but there is a need for effective therapy to be conducted to explore the role of physical rehabilitation interventions for people with CIP and CIM.

The second limitation is that this trial is planned to be carried out as a single-centre study and can, therefore, only be seen as a first or pilot study. This pilot trial is, however, adequately powered and funded. Further RCTs should, however, try to recruit further centres and hospitals to increase the clinical knowledge about physical rehabilitation interventions for people with ICUAW.

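### The sample size gives 80% power for an assumed 6-point FSS-ICU difference but about 65% for the 5 points called clinically important, and adjusting only for observed baseline differences leaves precision unused

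*Protocol article*

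**What the plan says.** All references are to the protocol article.

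- **Sample size.** The calculation "is based on a difference of 6 points in the primary endpoint of the FSS-ICU sum score" after two weeks of treatment, with means of 22 and 16, "assuming a SD of 10 in the FSS-ICU sum score", alpha 5%, power 80% and a two-sample t test. This gives 45 per arm, raised to 54 per arm (108 in total) for 20% dropout. The section says the literature offers no specific effect size for these interventions in this population and describes the 22 versus 16 as a theoretical assumption.
- **Statistical methods.** On the threshold of importance: "We will consider a minimum difference of 5 points of the FSS-ICU sum score" (range 0–35) between groups as clinically important. On adjustment: the groups are compared at baseline with t tests or Fisher's exact tests, and variables found to differ are treated as possible confounders and adjusted for afterwards.
- **Table 2.** FSS-ICU is scheduled at baseline (T0) and after two weeks (T1). The Informed consent section makes completed baseline tests a condition of randomisation.
- **Limitations.** "This pilot trial is, however, adequately powered and funded".

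The article neither gives the power at 5 points nor says why 6 rather than 5 was the target.

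**The concern.** The article has two between-group differences on one primary score: the one it is powered for and a smaller one that it calls important. A reader of the Limitations section will probably take the adequacy statement to cover any difference the trial regards as important. It does not cover differences between 5 and about 6 points.

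If the true difference were 5 points, the trial would miss it about 35 times in 100, not the 20 in 100 given under Sample size. Both arms are active treatments, so a modest difference and a non-significant result are realistic. Such a result could be read too confidently.

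The plan also has an unused means of narrowing the gap. The baseline value of the same score is usually a strong predictor of the two-week value, yet it enters the analysis only if the groups happen to differ on it. Whether a chance imbalance appears says little about how much residual variance the covariate would remove.

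**Working it through.** **Inputs.** From Sample size: difference 6, SD 10, alpha 0.05, power 80%, 45 evaluable and 54 enrolled per arm, 20% dropout. From Statistical methods: important difference 5. The sample-size text does not state sidedness. Two-sided is taken because the baseline comparisons are made "using two-tailed Student’s" t tests and because only the two-sided version reproduces 45; one-sided gives 35 by the normal approximation.

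**Formula.** Two-sample t test with n per arm: noncentrality = difference / (SD × √(2/n)), with 2n − 2 degrees of freedom. Power is the noncentral-t probability beyond the two-sided critical value.

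**Step 1: reproduce the plan's figure.** Solving for 80% power at 6/10 = 0.6 SD gives n = 44.6, so 45 per arm. At n = 45 the standard error is 10 × √(2/45) = 2.108, the noncentrality is 6/2.108 = 2.846 and the critical value is 1.987. Power is 80.4%. The plan's number is confirmed.

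**Step 2: the same design at 5 points.**

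| Analysed per arm | Basis | Power at 5 points | Power at 6 points |
|---|---|---|---|
| 43 | 54 × 0.8 = 43.2 | 63.0% | 78.5% |
| 45 | planned evaluable number | 65.0% | 80.4% |
| 54 | everyone randomised | 73.1% | 87.1% |

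At n = 45 the noncentrality for 5 points is 5/2.108 = 2.372. The normal approximation gives 66.0%.

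**Step 3: size of the gap.** The smallest true difference with 80% power at 45 per arm is 5.97 points. For 80% power at 5 points, either 64 evaluable per arm would be needed (solution 63.8) or the SD would have to be about 8.4.

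**Step 4: the effect of baseline adjustment.** With correlation r between baseline and two-week scores, the residual SD is 10 × √(1 − r²). The article gives no r, so a range is shown for 5 points.

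| Assumed r | Residual SD | Power, 45 per arm | Power, 43 per arm |
|---|---|---|---|
| 0.3 | 9.54 | 69% | 67% |
| 0.5 | 8.66 | 77% | 75% |
| 0.6 | 8.00 | 83% | 82% |
| 0.7 | 7.14 | 91% | 89% |

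The one degree of freedom spent on the covariate does not change these rounded figures. Power reaches 80% at r of about 0.55 with 45 per arm and about 0.58 with 43.

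**The case against.** **An expected effect and a smallest important effect are different quantities.** Sizing on the first when it exceeds the second is a recognised choice. The article never claims 80% power at 5 points, and what it does claim, 80% at 6, is delivered. This stands. A reader might infer that the calculation is wrong, that the two sections contradict each other or that the trial needs more patients; the text supports none of these. The rationale for 6 is thin, since the article itself reports no effect size in the literature, but a thin rationale is not an error.

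**An observed difference of 5 would be significant.** At 45 per arm and SD 10 the critical observed difference is 1.987 × 2.108 = 4.2 points. That is correct, but power concerns a true difference of 5, and around that value the observed difference would fall below 4.2 about one time in three.

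**The adequacy statement can be read against the only power calculation given.** It also follows a sentence presenting the trial as a first or pilot study. On that reading it is accurate for 6 points. What remains is that it names no difference while the article names a smaller one as important.

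**The Ethics and dissemination section might seem to make the same claim.** It says the study "seems to have enough power to detect meaningful determinants". The wording is hedged, does not mention FSS-ICU or 5 points, and does not clearly refer to the treatment comparison. It should not be used as support.

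**The gain from ANCOVA depends on an unknown correlation.** True: at r = 0.3 or 0.5, power at 5 points stays below 80%. The gain is therefore shown as a range. The case for adjustment does not need a particular value: any appreciable correlation improves precision, and the cost if there is none is one degree of freedom.

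**No passage plans to read a null result as showing no important difference.** Also true. That risk lies in how readers may take the result, which is why the wording changes are secondary.

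**Conclusion.** The point holds in a limited form. The sample size is correct for the 6-point difference it assumes. For the 5 points named as clinically important, power is about 65% at the planned 45 per arm, ranging from 63% (43 per arm) to 73% (all 54 analysed). This assumes SD 10, a two-sided 5% level and an unadjusted two-sample t test. The general statement of adequate power is therefore true only for differences of about 6 points or more.

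The part most worth acting on is the adjustment rule. By tying adjustment to observed baseline differences, the plan gives up precision that a prespecified baseline FSS-ICU covariate would provide. How much is unknown: about 69% to 91% power at 5 points for assumed correlations of 0.3 to 0.7, so adjustment narrows the gap but may not close it.

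**What to change.** 1. **Main change, Statistical methods.** Prespecify the primary FSS-ICU analysis as an ANCOVA of the T1 score on treatment group and the T0 FSS-ICU score. Let this replace adjustment triggered by baseline significance tests.
2. **Sample size.** State power at both differences for 45 per arm and SD 10: 80% at 6 points, about 65% at 5 points unadjusted. If a gain from adjustment is quoted, give the assumed correlation and a range.
3. **Limitations.** Restrict the statement of adequate power to the 6-point difference.

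**Cost.** One model specification and two wording changes. There are no extra patients, visits or measurements, because the baseline score is already scheduled. The power statement becomes less favourable.

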### Outcome measures

Primary efficacy endpoints are walking ability and activities of daily living.

We define our endpoint walking ability with a category of ≥3 on the Functional Ambulation Categories (FAC; 0–5 score range) [25–27]. We use this scale to measure walking ability because in a recent cohort study it has been shown to be a very feasible tool to describe the ability to walk in different settings, such as ICU, post-acute rehabilitation and also at follow-up [26].

We will use the Functional Status Score for the Intensive Care Unit Scored (FSS-ICU; 0–35 score range) [28] to measure elementary activities of daily living. We will use this scale because in a recent cohort study the FSS-ICU was also very feasible, reliable and also predictive (for important aspects of daily living) in different settings and stages such as ICU, post-acute rehabilitation and post-acute care [26].

Our secondary endpoints comprise scales with a comprehensive spectrum of impairments, activities and participation for this population (see Table 2). We will measure the ability to stand up by documenting the ability to stand up from a standardised chair independently (STS) [27]. We will measure muscle strength of the upper (shoulder, elbow and wrist) and lower limb (hip, knee and ankle) using the Medical Research Council (MRC) sum score and calculate and provide a MRC sum score for the upper and also for the lower limbs [1, 27, 29]. We will measure the handgrip strength for both hands using a hand dynamometer (Jamar handgrip dynamometer; Sammons Preston Rolyan, Bolingbrook, IL, USA) [27, 30–32]. We will use the Physical Function for the Intensive Care Unit Test-Scored (PFIT-S) [33] to measure specific ICU impairments. We will assess quality of life using the EQ-5D [34] and measure participation with the Reintegration to Normal Living Index (RNL-Index) [27, 35, 36]. All of these measures are frequently used in research and/or clinical practice dealing with this patient group. Table 2 gives a detailed overview of the variables used at each time point of study and the data collection schedule.

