All dependent (explanatory) variables will be first described in a univariate analysis and then selected for a multivariable model based on statistical significance [44–46]. In this process an explanatory variable has to be significant at the 0.2 level to be *entered* into the multivariate model [43]. To *remain* in the multivariate model an explanatory variable has to be significant at the 0.1 level [43]. We will first select explanatory variables from a list of all univariate analysis with the highest global chi-square score into our multivariable model [43]. We will use a graphical inspection and also evaluate whether the proportional hazard assumption for an explanatory variable is met [41]. We will, for the final model selection, compare the multivariate models (with remaining variables) on the global score chi-square statistic (best subset selection) and on the Akaike’s information criterion (AIC) performed [43]. The aim of our analysis is to *explain* the dependent variable (e.g. regaining walking function) by a multivariate Cox proportional hazard model with not too many variables (to prevent overfitting) [43]. The multivariate effects of explanatory variables in the final model will be expressed as hazard ratios (HR) with 95% CI [43]. We will use SAS/STAT 9.3 for all statistical procedures (SAS Institute Inc., Cary, NC, USA).

We will do an interim analysis for efficacy and ineffectiveness after half the patients have completed our study trial. The trial will be stopped if there is a statistically significant difference between the groups in one direction at an alpha level of 0.05 at this time point of recruitment.

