### Adverse event monitoring and reporting

All adverse events will be carefully monitored at every level of the FITonICU study. A Data Safety Monitoring Board provides oversight and meets after randomisation of every 20 newly recruited patients. All adverse events are reported immediately to the responsible physician and the board members are informed of all adverse events.

The Data Safety Monitoring Board and the research team (all authors) will be responsible for data safety and for the confidentially of recruited patients. The confidentiality of participants will be granted by using anonymous ID lists for all recruited patients. All patient data will be maintained and stored confidentially on a separate computer server.

The Data Safety Monitoring Board will do an interim analysis for safety of every 20 included and treated patients. The trial will be stopped:If there is a statistically significant difference in safety between the groups in one direction at an alpha level of 0.05 at this time point of recruitmentIf one of the interventions is associated with unexpected excessive adverse effects such as skin ulcerations, pulmonary embolism or deep vein thrombosis, or there are excessive withdrawalsIf the study recruitment is unsuccessful (e.g. 3 months without any recruitment) orIf other situations occur that might justify stopping this trial

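### The halfway efficacy look stops the trial at an unadjusted 0.05, which uses up the whole stated 5% alpha; with the final test also at 0.05, type I error for one endpoint is about 8.3%

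*Protocol article*

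**What the plan says.** All references are to the protocol article.

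- **Interim (Statistical methods, last paragraph).** There is to be an "interim analysis for efficacy and ineffectiveness after half the patients have completed our study trial". The stopping rule is: "The trial will be stopped if there is a statistically significant difference between the groups in one direction at an alpha level of 0.05". No boundary, alpha spending or reduced final level is given, and no endpoint is named.
- **Overall level (Statistical methods).** "The global alpha level will be set at 0.05 for all comparisons". The only multiplicity method is a Tukey-Kramer "alpha adjustment for multiple comparisons of the same outcome".
- **Endpoints (Outcome measures).** "Primary efficacy endpoints are walking ability and activities of daily living", measured by FAC of 3 or more and by FSS-ICU. Nothing says whether one or both must be significant, or in what order they are tested.
- **FSS-ICU hypothesis (Statistical methods).** The test is that "the sum score after 2 weeks of intervention and at follow-up will be statistically different between groups", which is non-directional.
- **Sample size.** 45 per arm are needed to detect 6 points with SD 10, 5% alpha and 80% power, with no allowance for an interim look; 108 are to be enrolled.

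**The concern.** A global alpha of 0.05 and an interim that may stop the trial at 0.05 cannot both hold if anything is tested afterwards. The first look uses the entire error allowance, and every later test at a positive level adds to it.

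The rule is mandatory and likely to act. Under the plan's own assumptions (6 points, SD 10), a t test at 0.05 with 22 to 27 patients per arm would stop the trial in about 49% to 58% of runs. In the stopped trials the mean estimated difference would be about 7.8 to 8.4 points against a true 6. A false positive is therefore more likely than stated, and a true effect would often be reported early and too large.

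Because the trigger endpoint is not named, either primary could be used to stop. That adds a second source of error, which has to be counted separately from the interim.

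**Working it through.** **Step 1: the plan's own figure.** Inputs from Sample size: difference 6, SD 10, two-sided alpha 0.05, power 80%, two-sample t test. The noncentral t calculation gives n = 44.6, so 45 per arm, with power 80.4%. The plan's 45 is reproduced. It is the figure for a fixed design with the full 5% spent at one final analysis.

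**Step 2: one endpoint, two looks.** With information fraction f at the interim, the two test statistics are bivariate normal with correlation √f, and

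type I error = 1 − P(|Z₁| < 1.96 and |Z₂| < 1.96).

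At f = 0.5 the correlation is 0.707 and the result is 0.0831: 5% at the interim plus 3.3% from trials that pass it and are falsely significant at the end. A t-test simulation with 22 and then 45 per arm gives 8.4%.

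| Information fraction | 0.3 | 0.4 | 0.5 | 0.6 | 0.7 | 0.85 |
|---|---|---|---|---|---|---|
| Type I error | 8.9% | 8.6% | 8.3% | 8.0% | 7.6% | 6.8% |

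The stopping rule's reference to one direction is ambiguous. Other readings at f = 0.5:

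- One-sided 0.05 at both looks: 8.0%.
- One-sided 0.05 in a prespecified direction at the interim, two-sided 0.05 at the end: 8.7%.
- One-sided 0.05 in either direction at the interim, two-sided 0.05 at the end: 12.5%.

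None gives 5%.

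**Step 3: two primaries, with the causes separated.** The correlation between the two primary test statistics is not in the document, so it is assumed over a range. At correlation 0 the values follow directly: without an interim 1 − 0.95² = 9.8%; with both endpoints at both looks 1 − (1 − 0.0831)² = 15.9%. The others come from simulation with 2 million replicates, taking either endpoint as sufficient.

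| Assumed correlation | No interim | Interim on FSS-ICU only, both at end | Either endpoint at both looks |
|---|---|---|---|
| 0 | 9.8% | 12.9% | 15.9% |
| 0.5 | 9.1% | 12.2% | 14.9% |
| 0.7 | 8.4% | 11.4% | 13.6% |
| 0.9 | 7.0% | 10.1% | 11.5% |

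The first column is due to the two primaries alone. Only the increase beyond it is due to the interim.

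**Step 4: boundaries that hold 5% for one endpoint** (one look at f = 0.5).

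| Boundary | Interim p | Final p |
|---|---|---|
| O'Brien-Fleming-type spending | 0.00305 | 0.0490 |
| Classic O'Brien-Fleming | 0.0052 | 0.0480 |
| Haybittle-Peto | 0.001 | 0.0498 |

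**Step 5: does a boundary on FSS-ICU suffice?** With 0.003 and 0.049 for FSS-ICU and walking ability still tested at 0.05 at the end, the overall error is 9.8%, 9.1%, 8.3% and 7.1% at correlations 0, 0.5, 0.7 and 0.9. It does not: a rule linking the two primaries is also needed.

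**The case against.** **The analysis plan may contain a boundary.** A published protocol may leave boundary details to that document. Here, however, the article states the interim level itself. An analysis plan could repair this only by overriding it.

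**Tukey-Kramer covers it.** It does not. With two groups there is one pairwise comparison, so it changes nothing, and it does not address repeated looks.

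**The final level is inferred.** This is true: 0.05 at the end is taken from the global alpha and the sample size calculation. But once 5% is spent halfway, any positive final level exceeds the total.

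**The information fraction may not be 0.5.** This stands in part. What counts as having completed the trial is not defined, and for walking ability, analysed as time to event, information depends on events. The error then moves between about 7% and 9%, never to 5%.

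Three stronger readings are tempting but not supported:

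- *The interim look raises the error to 11.5% to 16%.* Part of that comes from two unlinked primaries. The figure also needs either endpoint to suffice at both looks, which the plan does not state. If both had to be significant at the same look, the error would be about 0.5% at correlation 0 and 5.1% at 0.9; the plan does not state that rule either.
- *The look comes so late that most patients are already randomised.* This assumes completion means the 12-month visit. The article does not say so, and the stopping sentence also refers to a time point of recruitment. Only an undefined trigger can be claimed.
- *The safety rule has the same fault.* It also stops on a "statistically significant difference in safety between the groups in one direction at an alpha level of 0.05", at every 20 patients. False safety stopping does not inflate efficacy alpha. Its size depends on a test the article does not name: about 14% over five looks with a large-sample test, 4% to 7% with an exact test at 10% to 40% event rates. How readily to stop for safety is a trade-off, and no change is asked for.

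**Conclusion.** The plan contradicts itself. It states a global 5% and sets a mandatory interim rule that spends all of it before the final test. For one endpoint the type I error is about 8.3%, assuming two-sided tests at 0.05 at both looks and half the information at the first; it is about 7% to 9% for information fractions from 0.85 to 0.3. This needs no assumption about correlation or about how the primaries combine.

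The unnamed trigger endpoint and the unlinked primaries are a second, separate defect, worth 7.0% to 9.8% without any interim. Together the two defects reach about 11.5% to 16%, if either endpoint suffices at both looks and the correlation lies between 0.9 and 0. Testing FSS-ICU at follow-up as well could add to this and is not counted.

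**What to change.** 1. Base the efficacy look on FSS-ICU at T1 only, and make it when the first 54 patients (half of 108) have T1 data. This names the endpoint, defines the trigger and keeps the information fraction near 0.5.
2. Replace the 0.05 rule with a two-sided group-sequential boundary: O'Brien-Fleming-type spending (stop at p<0.003, final test at 0.049) or Haybittle-Peto (stop at p<0.001, final test at about 0.0498).
3. State how FSS-ICU and walking ability share the 5% at the end, either by a hierarchy or by an alpha split. State also at what level walking ability is tested if the trial stops early.

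**Cost.** The changes are to wording only. The boundary lowers FSS-ICU power at 45 per arm from 80.4% to 80.2% and makes an early efficacy stop less likely. A hierarchy with FSS-ICU first costs FSS-ICU nothing further. A split costs more: in a normal approximation the expected statistic is 0.6 × √(45/2) = 2.85, so power is Φ(2.85 − 1.96) = 81% at 0.05 and Φ(2.85 − 2.24) = 73% at 0.025. An even split would therefore need more patients to keep 80%.
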